**3) Subgroup analyses**			
a) High v/s low severity	Greater effect in low severity.		
b) Motivational level	Higher motivation intensifies the treatment effect.		
c) Educational level	Higher education intensifies the treatment effect.		
d) Male v/s female	Sex interacts with treatment effect.		
**4) Sensitivity analyses**			
a) Per-protocol analysis			a) *T* test/chi-squared
b) Adjustment for baseline variables			b) Linear model (multivariate regression)
c) Missing data imputation			c) Multiple imputation (missing-at-random assumption)

### Interim analyses {21b}

Not applicable. We do not expect that this intervention added to usual care increases the rate of adverse events or complications. On the other hand, the recruitment rate and sample size make interim analyses impractical.

### Methods for additional analyses (e.g., subgroup analyses) {20b}

Linear models with the appropriate interaction factors will deliver the subgroup analyses. We will examine the residuals to check for model assumptions and common problems with the errors, the predictors, and the model structure. If necessary, robust regression methods or transformations will be used.

### Methods in analysis to handle protocol non-adherence and any statistical methods to handle missing data {20c}

For the analysis of missing data, we will follow the missing-at-random assumption, which allows valid analysis independently of the missing value mechanism. We assume, therefore, that missingness is associated with the baseline alcohol use pattern after conditioning on covariates, which is a reasonable assumption since higher alcohol usage leads to treatment failure and reduced follow-up. In this scenario, we will use a multiple imputation method to handle missing data.

On the other hand, to prevent attrition bias, outcome data from all randomized participants will be analyzed according to the group they were allocated, regardless of protocol adherence.

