**Methods:**

A parallel-group, single-blinded, severity-stratified, randomized clinical trial will test the superiority of BMT over enhanced usual care. Eligible participants will be those seeking treatment and who fulfill DSM-V criteria for alcohol use disorder and criteria for harmful alcohol use. With an estimated a loss to follow-up of 20%, a total of 182 participants will be recruited and equally randomized to each treatment group. The intervention group will receive an adaptation of the motivational enhancement therapy, as manualized in Project MATCH. This treatment consists of four 45-min sessions provided by a general psychologist with at least 3 years of primary care experience. The primary outcome is the change from baseline in the drinks per drinking day during the last 90 days, which will be captured using the Timeline Follow Back method. Secondary outcomes will describe the changes in alcohol use pattern, motivational status, and severity of the disorder.

All participants will be analyzed according to the group they were allocated, regardless of the treatment actually received. Mean differences (MD) will be computed for continuous outcomes and relative risks (RR) and RR reductions (RRR) for dichotomous results. Linear models will deliver the subgroup analyses. Missingness is assumed to be associated with the baseline alcohol use pattern and severity, so a multiple imputation method will be used to handle missing data.

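### The text handles missing data by multiple imputation, Table 1 makes it only a sensitivity analysis behind a plain t test, and the sentence justifying missing-at-random is false

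*Protocol article*

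**What the plan says.** Four places in the protocol article bear on this.

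- **Abstract, Methods.** Missingness is linked to baseline alcohol use pattern and severity, "so a multiple imputation method will be used to handle missing data". Nothing limits this to a secondary role.
- **Section {20c}.** It adopts MAR with the statement "we will follow the missing-at-random assumption, which allows valid analysis independently of the missing value mechanism". It then ties missingness to the baseline use pattern after conditioning on covariates, on the ground that "higher alcohol usage leads to treatment failure and reduced follow-up", and concludes: "In this scenario, we will use a multiple imputation method to handle missing data". It adds that "outcome data from all randomized participants will be analyzed according to the group they were allocated". Section {18b} likewise commits to including everyone, in line with intention to treat.
- **Table 1, primary row.** The method for drinks per drinking day (DDD) at 6 months is a t test. Imputation is not mentioned.
- **Table 1, block "4) Sensitivity analyses".** Three items are listed: a per-protocol analysis, adjustment for baseline variables, and imputation under MAR.

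Section {14} expects 20% loss to follow-up.

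**The concern.** Listing imputation as a sensitivity analysis makes sense only if the primary analysis is not imputed. Table 1 therefore implies a primary result from observed outcomes alone, while the abstract and section {20c} imply an imputed one covering everyone randomised. Both are described as the plan. With a fifth of outcomes expected to be missing the two can differ, and the choice between them could be made after the data are seen.

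The false MAR sentence adds to this. If MAR really gave validity whatever the mechanism, there would be no reason to examine departures from it, and none of the three listed sensitivity analyses does so.

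**Working it through.** **1. The passages side by side**

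| Place | Role of multiple imputation | Participants in the primary comparison |
|---|---|---|
| Abstract, Methods | The method for missing data | All, as allocated |
| Section {20c} | The method for missing data | All randomised, as allocated |
| Section {18b} | Not mentioned | All |
| Table 1, primary row | None; t test | Those with an observed outcome |
| Table 1, block 4 | Sensitivity analysis | (not primary) |

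The first three rows cannot be reconciled with the last two unless the t test is meant to be run on imputed data. In that case the block 4 entry has no function.

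**2. How many participants are involved**

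Inputs from section {14}: 91 per group, 182 in total, 20% loss.

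- Completers per arm: 91 × (1 − 0.20) = 72.8, about 73.
- Randomised participants outside an unimputed t test: 182 × 0.20 = 36.4, about 36.

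**3. When the completers' t test is biased**

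Let p be the share of low-severity participants among all randomised and p_c their share among completers. Let Δ_L and Δ_H be the treatment effects in low and high severity. If loss depends on severity alike in both arms, then

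bias of the completers' difference = (p_c − p) × (Δ_L − Δ_H).

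This is zero if loss is unrelated to severity or if the effect is the same at both levels. The article supposes neither: the abstract links missingness to severity, and Table 1, block 3, hypothesises a greater effect in low severity. If more severe participants are lost (p_c > p) and that hypothesis is right, the bias is upward.

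The sign is not secure, however. Section {14} expresses the expected reductions as percentages of baseline (14% and 40%). If reductions are proportional, heavier drinkers have the larger absolute effect. Losing them then biases the estimate downward: simulation gave 2.67 to 2.83 against 2.99, with about 21–22% loss.

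**4. Does validity under MAR depend on the mechanism?**

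Inputs from section {14}: baseline 11.5, EUC 9.89, BMT 6.9, SD 6.29, 20% loss; true difference 9.89 − 6.9 = 2.99. Assumptions not in the article: baseline-to-6-month correlation 0.3 or 0.5, and dropout log-odds slope 0.5 or 1.0 per SD. The effect is additive. The MAR estimate is a within-arm regression on baseline, the large-sample equivalent of imputing from baseline.

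| What drives dropout | Completers' difference | MAR estimate |
|---|---|---|
| Baseline drinking, both arms | 2.98–3.00 | 2.98–3.00 |
| 6-month drinking, both arms | 2.64–2.88 | 2.67–2.89 |
| 6-month drinking in EUC, baseline in BMT | 2.22–2.68 | 1.98–2.53 |
| 6-month drinking in BMT, baseline in EUC | 3.30–3.75 | 3.46–4.00 |

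Only the first row recovers 2.99, so validity does depend on the mechanism.

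**5. Scenarios for the lost 20%**

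The observed completers' difference is taken as 2.99, and only the assumed mean of the lost participants changes.

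- Lost BMT at the EUC mean, lost EUC at the EUC mean: 9.89 − (0.8 × 6.9 + 0.2 × 9.89) = 9.89 − 7.50 = 2.39.
- Lost BMT at baseline, lost EUC at the EUC mean: 9.89 − (0.8 × 6.9 + 0.2 × 11.5) = 9.89 − 7.82 = 2.07.
- Lost EUC at baseline, lost BMT at the BMT mean: (0.8 × 9.89 + 0.2 × 11.5) − 6.9 = 10.21 − 6.9 = 3.31.

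These show what is possible in either direction. They do not estimate the bias.

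**The case against.** **The stated reason for dropout.** A reader might infer that it proves the data are missing not at random. It does not. Section {20c} ties missingness to baseline use, and the clause about higher usage carries no time point. If it means baseline use, with treatment failure and reduced follow-up as parallel consequences, the data are MAR once baseline use is in the imputation model. What stands is narrower: treatment failure occurs after randomisation, so loss related to the outcome itself remains plausible.

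**The t test under the protocol's own premise.** A reader might also call the completers' t test invalid even if baseline drinking drives dropout. That is too strong. With the same dropout pattern in both arms and an additive effect it is unbiased (first row of the table in step 4). Bias needs dropout that differs by arm, or effect modification.

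**Direction.** Nor do the documents support saying that the error favours BMT. Steps 3 to 5 give results on both sides of 2.99.

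**The MAR sentence as shorthand.** It may be loose wording for ignorability: under MAR the mechanism need not be modelled. The next sentence does state an assumption about the mechanism, so the authors do not plan as if any mechanism would do. That makes it a wording correction, but the sentence as printed is still wrong.

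**Left to a fuller document.** Imputation details and analyses departing from MAR are commonly left to a full protocol or analysis plan, and section {31c} points to material not shown here. Their absence alone would not be a finding. The contradiction over the primary analysis is different, because it lies within the article.

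**Conclusion.** The plan is wrong as written on two points. The article gives two incompatible primary analyses, and the one in Table 1 would leave about 36 of 182 randomised participants out of a comparison that is said to include all of them. The statement about MAR is false.

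The size and sign of any resulting bias are unknown. The range of 2.07 to 3.31 around 2.99 rests on assumed means for the lost participants, and the simulated ranges rest on assumed correlations and dropout slopes. Loss of treatment failures that is not at random is a plausible risk, but the article does not state it. None of the listed sensitivity analyses would detect it.

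**What to change.** 1. In Table 1, make the multiply imputed comparison the primary analysis of DDD. Impute separately by arm, using at least baseline DDD, baseline SDSS-DAYS and site. Section {18b} mentions two follow-up sessions but does not say that drinking is recorded at the earlier one, so add those data only if they are collected.
2. Move the completers' t test to the sensitivity block.
3. Replace the MAR sentence in section {20c} with one saying that validity depends on missingness being explained by the variables in the imputation model.
4. Add one delta-adjusted (tipping-point) sensitivity analysis, with shifts in the imputed values applied in either arm, because the direction is not known in advance.

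The cost is an edit to Table 1, one paragraph and a few more lines of R. Baseline DDD, SDSS-DAYS and site are already recorded for the outcome and the stratified randomisation, so no new data are needed. Section {25} treats changes to the statistical analysis as requiring a formal amendment to the ethics committee, so the correction should go through that route.

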### Plans to give access to the full protocol, participant level-data, and statistical code {31c}

The full protocol, dataset, and statistical code are available in the Open Science Foundation repository, DOI 10.17605/OSF.IO/6BA3W

## Oversight and monitoring

### Composition of the coordinating center and trial steering committee {5d}

This trial will be conducted and monitored by a small research team made up of the authors and the support staff. This team includes a person with data management training who will oversee data collection and integrity and a general coordinator to handle daily operations at the sites.

### Composition of the data monitoring committee, its role and reporting structure {21a}

Not applicable. This trial is of relatively short duration and presents minimal risks for participants since BMT is not known to have adverse effects on clients. Any typical emergency situations will be managed as usual in the health care context. For these reasons, it seems unnecessary to have a formal data-monitoring committee (i.e., a multidisciplinary group of people independent from the trial researchers that decide on trial modification or suspension).

### Adverse event reporting and harms {22}

The brief motivational therapy is not supposed to increase health risks in clients; however, due to the behavioral nature of the alcohol use disorder, it is expected that some common problems could arise in the participants. High-risk events, such as suicidal ideation or behavior, violence and aggression to others, increase in depressive symptoms or anxiety, severe intoxication, or withdrawal symptoms, will all be managed with a crisis intervention delivered in the health center in accordance with local protocols. Close coordination between the study therapists and the rest of the health team will be encouraged through all protocol execution so that crisis protocols can be activated when necessary.

The study therapists will be responsible for assessing the participant when an adverse event is suspected and, if confirmed, will contact the trial coordinator and the local organization to mobilize the required resources (e.g., medical assessment, referral to the emergency room, and contact to a family member). The participants will have access to a centralized phone number where they can contact their therapist for help in case of emergency issues regarding treatment.

The trial coordinator will complete a report with the details of the event, including the diagnosis, management, and harms to the participant.

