### Intervention description {11a}

#### BMT

Participants in the intervention group will receive the BMT, which is a PC adaptation of the MET as manualized in the Project MATCH [19]. This treatment consists of four 45-min sessions, provided by a psychologist at weeks 1, 2, 6, and 12. The first three sessions, occurring during the first 6 weeks, are more active regarding the behavioral change, while the last session functions as closure and review of the process. If a participant asks for more support, they will be able to attend up to two extra sessions before the last one.

The main adaptations to the original Project MET manual are:
The translation into Chilean Spanish.An update of MI concepts used throughout the manual using the last edition of the MI reference book.The addition of companion training material that includes a demonstrative video and practical exercises on the MI strategies.A personalized feedback procedure based on the evaluation used in the trial and the local epidemiological situation.The addition of information on additional resources available in the PC center and the community to be included in the “menu of options.”The addition of a module regarding the coordination of health services in the Chilean PC context. This supplementary material is meant to facilitate the participants’ access to services complementary to BMT within the PC center (i.e., social services, medical services, among others).

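### Adverse event assessment is assigned to therapists whom only the BMT arm sees, with no defined route for EUC events, so reported events would be ascertained unequally and unblinded

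*Protocol article*

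**What the plan says.** The section Adverse event reporting and harms {22} sets out one chain. On assessment: "The study therapists will be responsible for assessing the participant when an adverse event is suspected". If the therapist confirms the event, the therapist contacts the coordinator, and then: "The trial coordinator will complete a report with the details of the event, including the diagnosis, management, and harms to the participant". Participants may also call "a centralized phone number where they can contact their therapist for help in case of emergency issues regarding treatment". No other assessor or reporter is named. One further link is mentioned: "Close coordination between the study therapists and the rest of the health team will be encouraged through all protocol execution". Its stated purpose is that crisis protocols can be activated.

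Contact with a study therapist is fixed elsewhere. Under Intervention description {11a}, BMT: "Participants in the intervention group will receive the BMT", and "This treatment consists of four 45-min sessions, provided by a psychologist at weeks 1, 2, 6, and 12", with up to two extra sessions on request. Selection and supervision of the providers describes these professionals as recruited and trained to deliver BMT. Enhancement of usual care gives a brochure to all participants and information to the physicians; it assigns no study therapist to the EUC arm.

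Under Who will be blinded {17a}, a blinded research assistant does the follow-up assessments, while therapists and participants know the allocation. Section {18b} mentions two follow-up sessions.

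On risk, the section on the data monitoring committee {21a} says the trial "presents minimal risks for participants since BMT is not known to have adverse effects on clients".

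**The concern.** The harms section expects suicidal ideation, violence, severe intoxication and withdrawal to arise from the disorder itself, so they can occur in either arm. The person charged with assessing them sees one arm four to six times and has no scheduled contact with the other. The explanation of the comparator {6b} adds to the imbalance: over 80% of AUD cases are assumed to be waiting for specialist services with little non-specific care in the meantime. The arm without a study therapist may thus have few other contacts through which an event would surface.

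Two things are at stake. First, a count of reported events by arm would mix the true difference with the difference in observation, and the trial is meant to inform whether Chilean primary care adopts BMT. Second, events in EUC participants have no defined path to trial oversight, whether or not a safety table is ever produced.

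**Working it through.** No sample size, power or event figure in the plan is at issue, so there is nothing to reproduce. The check has two parts.

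**1. Tracing the chain by arm**

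| Step | BMT arm | EUC arm |
|---|---|---|
| Scheduled contact with a study therapist ({11a}) | 4 sessions, up to 6 | none stated |
| Assessor of a suspected event ({22}) | the participant's therapist | a study therapist in name; none is assigned |
| Participant's own route ({22}) | phone line to the therapist | same line, but no therapist to reach |
| Health team ({22}) | coordination encouraged | coordination encouraged; no reporting duty stated |
| Research assistant at two follow-ups ({17a}, {18b}) | no event task stated | no event task stated |
| Assessor's knowledge of allocation ({17a}) | known | known |

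The harms wording speaks of participants in general, so it does not exclude EUC. But each named step runs through someone whom only BMT participants see. Followed as written, the procedure makes ascertainment depend on allocation.

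**2. Illustration of size**

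From the plan: 91 participants per arm (Sample size {14}). Assumed, because the plan gives no such figures: a true risk *p*, equal in both arms, of 5%, 10% or 20%; capture under BMT *s*_B = 90%; capture under EUC *s*_E = 90%, 50% or 25%.

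Expected recorded events in an arm = 91 × *p* × *s*. Apparent risk ratio = (*p* × *s*_B)/(*p* × *s*_E) = *s*_B/*s*_E, which does not depend on *p*.

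- *s*_E = 90%: 0.90/0.90 = 1.0
- *s*_E = 50%: 0.90/0.50 = 1.8
- *s*_E = 25%: 0.90/0.25 = 3.6

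| True risk in both arms | BMT recorded (90%) | EUC recorded (50%) | EUC recorded (25%) |
|---|---|---|---|
| 5% | 91 × 0.05 × 0.90 = 4.10 | 91 × 0.05 × 0.50 = 2.28 | 91 × 0.05 × 0.25 = 1.14 |
| 10% | 91 × 0.10 × 0.90 = 8.19 | 91 × 0.10 × 0.50 = 4.55 | 91 × 0.10 × 0.25 = 2.28 |
| 20% | 91 × 0.20 × 0.90 = 16.38 | 91 × 0.20 × 0.50 = 9.10 | 91 × 0.20 × 0.25 = 4.55 |

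At a true risk of 10% the spurious risk difference is 0.09 − 0.05 = 0.04 with 50% EUC capture, and 0.09 − 0.025 = 0.065 with 25%. With equal capture it is zero.

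**The case against.** A reader might infer that therapists alone detect events, that EUC harms go unrecorded, and that no between-arm safety comparison is possible. The document supports none of these. It assigns assessment once an event is suspected and does not say who raises the suspicion. The coordinator's report is not confined to BMT, and contact between therapists and the health team could bring in some EUC events. Some harm-related data are collected in both arms by the blinded assistant: DrInC-2R consequences, SDSS symptoms and the drinking calendar. All of that stands. What remains is that the health-team link is described for activating crisis protocols, not for reporting, and that those instruments do not record events such as suicidal ideation.

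No between-arm safety analysis is announced; Table 1 has none. So the bias threatens a comparison that someone may make, not one that is planned. That stands too, though the missing EUC route matters for oversight in any case.

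The likely direction, more events recorded under BMT, would not tend to hide a harm of BMT, and the case against a monitoring committee in {21a} rests on short duration, what is known of BMT and usual emergency care, not on event counts in the trial. It would therefore be too strong to say that the no-added-harm premise cannot be checked. The defect is that an observed excess could not be interpreted.

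Finally, the article condenses a fuller protocol that is not shown, so missing forms or detailed questions are no fault. This point does not rest on silence alone: the article does state a harms procedure, and that procedure names an assessor whom only one arm sees.

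**Conclusion.** The point holds in a limited form. The stated procedure places adverse event assessment with therapists whom only BMT participants see, and it defines no route for an EUC participant's event to reach the coordinator. Ascertainment is therefore unequal and unblinded. EUC events are likely to be under-recorded, and any comparison of reported events would tend to show a spurious excess under BMT.

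The size is unknown. The apparent ratios of 1.8 and 3.6 rest on assumed capture of 90% under BMT against 50% and 25% under EUC, with equal true risk; they show how the mechanism works and are not estimates. The direction assumes that more frequent contact leads to more recorded events.

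Primary and secondary efficacy inference is not affected. The harms procedure should still be corrected, because the correction is cheap and the gap covers events that the section itself expects.

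**What to change.** Amend Adverse event reporting and harms {22} as follows. The changes concern recording only; clinical handling of events stays as the document has it.

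1. Add one fixed checklist of the high-risk events already listed there. The blinded research assistant gives it in identical form to both arms at the two existing follow-up sessions, after all outcome instruments for that session are complete. Participants are reminded beforehand not to disclose their allocation. Events go onto the same coordinator report form in both arms.
2. State a route by which the primary care health team notifies the coordinator directly of an event in a participant of either arm.
3. State that any between-arm safety statement uses only the checklist records. List therapist-reported events separately, as descriptive data for the BMT arm.

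The cost is a few minutes per follow-up session and one short form, with no added visits or staff. The downside is a small added risk of unblinding, since a participant describing an event may mention a therapist. Asking last protects that session's instruments, but unblinding at the first follow-up could carry over to the 6-month assessment if the same assistant does both. The reminder reduces this risk but does not remove it.
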